#### Descriptive analyses of baseline factors

The distribution of infant characteristics and network-level broad organizational structural features will be summarized as counts and percentages for categorical variables and using the mean and standard deviation, or the median and interquartile range for continuous variables. The data will be compared among all networks using the Chi-square test for categorical and ANOVA F-test or Mood’s median test for continuous variables.

#### Comparisons between networks

For the primary composite outcome, each of its components and the additional secondary outcomes, initial crude rates, and associated 95% and 99% confidence intervals will be calculated and graphically displayed using ‘caterpillar plots’ to visually identify differences between networks. To adjust for multiple baseline characteristics, standardized outcome ratios will be computed using the ‘indirect standardization’ approach. Each network’s observed rate will be compared with the expected rate based on the total sample from all other networks to identify networks with rates significantly above or below average. For each outcome, the expected number of events will be computed as the sum of predicted probabilities from a multivariable model (logistic regression or zero inflated negative binomial models based on data distribution) derived using data from all other networks with adjustment for confounders. Network standardized outcome ratios will be graphically displayed using ‘funnel’ plots with 95% and 99% prediction intervals for comparison between networks.

A global comparison, as well as pair-wise comparisons between networks, will be performed using multivariate regression models adjusted for confounders. Statistical models will employ generalized estimating equations to adjust analyses for clustering of infants within networks. In addition, hierarchical random-effects regression models will be used to allow for variation at the network and unit level. Statistical significance will be evaluated by applying a Bonferroni correction to account for multiple pair-wise comparisons.

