### Comparisons of neonatal outcomes between networks

#### Outcomes

The primary outcome for comparison between the networks will be a composite indicator of mortality or any of the four major neonatal morbidities (severe neurological injury, severe ROP, NEC, and BPD). Mortality will be defined as death due to any cause prior to discharge home. Severe neurological injury will be defined as ≥ stage 3 intraventricular hemorrhage (IVH) with ventricular dilatation according to the criteria of Papile et al. [38], or parenchymal injury (including periventricular leukomalacia) with or without IVH. Severe ROP will be defined as ≥ stage 3 according to the International Classification [39], or need for laser surgery or intraocular injections of anti-vascular endothelial growth factor agents. NEC will be defined as ≥ stage 2 according to Bell’s criteria [40] and BPD as oxygen requirement at 36 weeks post-menstrual age [41].

Secondary outcomes to be compared among iNeo member networks will include the individual morbidities of the composite outcome, as well as nosocomial infection defined as culture-proven sepsis (blood or cerebrospinal fluid positive for pathogenic organism) at >3 days or 72 hours postnatal age [42], patent ductus arteriosus requiring pharmacological treatment and/or surgical ligation, receipt of delivery room cardiopulmonary resuscitation, air leak syndrome, and resource utilization (length of stay and length of respiratory support). To account for potential differences in practices regarding discharge home and transfer to Level 2 community units, additional analyses will compare mortality by Day 28 after birth. All outcomes will be expressed as ratios with the denominator equal to all admissions to participating NICUs.

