#### Statistical power for outcome comparisons

With retrospective data from 251 NICUs collected over four years (2007–2010), analyses (two-sided tests) comparing Canada (10,800 admissions) with all other networks (82,800 admissions), for example, will be able to detect rate differences of 0.004 to 0.02 for a range of outcome rates (1% to 40%) with statistical power of 80% assuming 5% type I error rate. Similar analyses comparing Canada with one other network (3,200 to 30,800 admissions) will be able to detect rate differences of 0.007 to 0.03.

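### For length of stay and respiratory support, the sum of predicted probabilities is not an expected number of days, so the standardised ratio would not centre on 1

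*Protocol article*

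**What the plan says.** The rule stands in the protocol article under *Comparisons between networks*. That section covers every outcome: "For the primary composite outcome, each of its components and the additional secondary outcomes, initial crude rates, and associated 95% and 99% confidence intervals" come first, and then "standardized outcome ratios will be computed using the ‘indirect standardization’ approach". The expected value for those ratios is stated once, for each outcome, as a number of events "computed as the sum of predicted probabilities from a multivariable model (logistic regression or zero inflated negative binomial models based on data distribution"), with the model fitted to all other networks and adjusted for confounders.

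The list under *Outcomes* includes "resource utilization (length of stay and length of respiratory support") among the secondary outcomes. The same section sets the scale: "All outcomes will be expressed as ratios with the denominator equal to all admissions to participating NICUs". No other section gives a separate expected value for the two durations.

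**The concern.** Indirect standardisation needs observed and expected values in the same unit, so that a network performing as predicted has a ratio of 1. For a yes/no outcome the sum of predicted probabilities is the expected count, and the rule works. For a number of days the expected value is a sum of predicted means. Any probability taken from the same model lies between 0 and 1, so its sum counts infants at most.

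Two secondary outcomes are at stake. The ratio is meant to show which networks lie above or below average. The *Care-provision factors* section then uses each secondary outcome to pick out the best-performing networks and those with most room to improve. A ratio with no reference value of 1 cannot support the first reading, and would be a poor guide to the second.

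**Working it through.** The article gives no figure for this formula, so there is nothing of its own to reproduce. The check is algebra, followed by an illustration.

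**Inputs from the article.** One rule for all outcomes, with logistic or zero-inflated negative binomial models (*Comparisons between networks*). Two duration outcomes (*Outcomes*). Network size from *Statistical power for outcome comparisons*: "comparing Canada (10,800 admissions) with all other networks (82,800 admissions"). The 10,800 agrees with Table 1: 2,700 a year × 4 years.

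**Assumed inputs.** The article gives no mean durations or model parameters. Below, π is the zero-inflation probability, μ the mean of the negative binomial part and k its dispersion parameter. Their values are assumptions chosen to show a range.

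**Step 1, which outcomes the count model can serve.** The composite, its components, day-28 mortality, nosocomial infection, treated patent ductus, delivery-room resuscitation and air leak are all yes/no per infant. Only the two durations are clearly not. The article does not make this link itself. It is an inference, but the outcome list leaves no other plausible target.

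**Step 2, binary outcomes.** With predicted probability p for each infant, the expected count is Σp. The stated rule is correct.

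**Step 3, durations.** Under a zero-inflated negative binomial model:

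- expected days per infant = (1 − π)μ
- probability of any days, P(Y>0) = (1 − π)[1 − (k/(k+μ))^k]

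The first is in days; the second is at most 1. If N infants perform exactly as predicted, total days are N(1 − π)μ, and the ratio to the sum of P(Y>0) is μ/[1 − (k/(k+μ))^k]. That is the mean number of days among infants with any. Such a denominator adjusts for the chance of having any days, not for how many. Dividing both sides by all admissions, to turn totals into rates, leaves the ratio unchanged.

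**Step 4, numbers for N = 10,800.** First row in full: (0.8/10.8)^0.8 = 0.1247; P(Y>0) = 0.8 × 0.8753 = 0.7003; × 10,800 ≈ 7,563. Expected days = 10,800 × 0.8 × 10 = 86,400. Ratio = 86,400/7,563 = 11.4.

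| π | μ | k | Expected days | Sum of P(Y>0) | Days ÷ sum of P(Y>0) | Days ÷ sum of predicted means |
|---|---|---|---|---|---|---|
| 0.2 | 10 | 0.8 | 86,400 | 7,563 | 11.4 | 1.0 |
| 0.3 | 20 | 0.8 | 151,200 | 7,002 | 21.6 | 1.0 |
| 0.1 | 40 | 1.5 | 388,800 | 9,653 | 40.3 | 1.0 |
| 0.05 | 60 | 2 | 615,600 | 10,249 | 60.1 | 1.0 |

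The text does not say which probability from the count model is to be summed. If it were π, the sums would be 2,160, 3,240, 1,080 and 540, and the ratios 86,400/2,160 = 40, 151,200/3,240 = 46.7, 388,800/1,080 = 360 and 615,600/540 = 1,140. No choice gives 1.

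**Step 5, what does not depend on the assumptions.** Any sum of one probability per infant is at most N. For a network performing as predicted, the literal ratio is therefore at least its mean days per admission.

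**The case against.** The strongest reply is that this is shorthand. The sentence speaks of events, and a stay is not an event, so it can be read as written for the yes/no outcomes. The sentence before it compares an observed rate with an expected rate, which presupposes a common scale. The count model is never tied to the durations in so many words. If the rule were followed literally, all eight networks would show ratios far from 1 and the slip would be seen at once. The crude rates, the adjusted global and pair-wise regressions and the hierarchical models do not use this sum.

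Much of this stands, and it limits the practical weight. It does not remove the point. The rule is stated for each outcome and names the count model inside the same formula, and nothing else in the article covers the durations. A condensed article may leave detail to a fuller document, but this is a formula that is stated and does not fit one of its own models.

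A reader might also infer more than the article supports:

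- **That zero inflation is wrong, or not identified, for length of stay.** The article never assigns that form to length of stay; it leaves the choice to the data. Deaths or transfers on the day of admission may be recorded as zero days, and the coding is not given.
- **That the eight models would be handled inconsistently.** Nothing says so, and the data are compiled at one coordinating centre.
- **That the funnel-plot limits are wrong for days.** The article says only that 95% and 99% prediction intervals will be shown. How they are calculated, and which duration model is preferred, can be left to the analysis plan.

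**Conclusion.** The expected-value formula is wrong as written for the two duration outcomes and right for all the others. Followed literally, it sets days against at most one unit per infant. The ratio for a network performing as predicted would then be about 11 to 60 under the assumed settings when the probability of any days is summed, instead of 1.

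Those sizes rest on assumed parameters and illustrate the scale error; they do not forecast a published result. It would be tempting to say that the reported ratios will be wrong by such a factor. The article does not support that, because an analyst would probably see the mismatch and sum predicted means. The conclusion also rests on the inference that the count model is meant for the durations. This is a minor wording correction, with no consequence for the primary comparison.

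**What to change.** In *Comparisons between networks*, replace the single rule with two:

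- **Binary outcomes:** expected value = sum of predicted probabilities.
- **Duration outcomes (length of stay, length of respiratory support):** expected value = sum of predicted mean days, which is (1 − π)μ per infant under a zero-inflated negative binomial model.

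Let the expected value refer to events or days, not events alone, and name the two durations as the outcomes for which the count model is intended. The cost is one or two sentences, with no new data and no change to any binary outcome.

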### Network objectives

The specific aims of iNeo are to:

– 1. Compare outcomes for infants born with VLBW (weighing <1500 g) and VPT (<32 weeks gestation) among eight national neonatal networks spanning nine countries.

– 2. Identify site-level physical, human, and environmental characteristics, as well as care practices that are associated with variations in outcomes.

– 3. Identify clinical and organizational practice improvements relevant to each network.

– 4. Implement and continually evaluate the impact of evidence-based clinical and organizational practice changes in NICUs within the iNeo networks.

The establishment of the iNeo collaboration will enable the following: i) collection and integration of individual-level data from population-based networks on outcomes, characteristics, practices, and culture of the member sites; ii) evaluation of the impact of practice and outcome variations to identify the best models of health service delivery (incorporating medical and other extraneous factors); iii) feedback to units of their standing in reference to each and all other networks; iv) empowerment of units to embrace implementation of evidence-based practice changes for quality improvement; and v) performance of ongoing cycles of translating knowledge-to-action through continuous auditing. Ultimately, this will improve outcomes for VLBW infants across the iNeo member networks.

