### Participating networks

The following neonatal networks have agreed to participate in the iNeo project: Australia-New Zealand Neonatal Network (ANZNN), Canadian Neonatal Network (CNN), Israeli Neonatal Network (INN), Neonatal Research Network of Japan (NRNJ), Spanish Neonatal Network (SEN1500), Swedish Neonatal Quality Register (SNQ), Swiss Neonatal Network (SNN), and UK Neonatal Collaborative (UKNC) (see Table 1). Overall, this project will be collecting data from a total of 251 NICUs in nine countries caring for approximately 23,000 to 24,000 VLBW neonates per year. All the participating networks have a common mandate to collect, analyze, and benchmark performance and outcomes of their respective NICUs. We have carefully avoided networks that only include highly specialized units in order to obtain robust population-based estimates. All participating networks have confirmed the feasibility of data collection from >75% of all VLBW and VPT infants born within their country. The approximately 25% of infants missing from some of the networks are those considered to be at the higher end of maturity (>1300 g birth weight or >30 weeks gestation) who do not require intensive care support. These infants are relatively stable and do not represent a significant burden to NICUs or health care services in general.

**Table 1 T1:** Characteristics of networks participating in the International Network for Evaluating Outcomes of Neonates (iNeo)

**Network**	**Australia and New Zealand Neonatal Network**	**Canadian Neonatal Network**	**Israeli Neonatal Network**	**Neonatal Research Network Japan**	**Spanish Neonatal Network**	**Swedish Neonatal Quality Register**	**Swiss Neonatal Network & Follow-****Up Group**	**UK Neonatal Collaborative**
Country	Australia and New Zealand	Canada	Israel	Japan	Spain	Sweden	Switzerland	UK (England)
Level III NICUs in the country	23 + 6	30	23	93	n/a	7	9	45
Level III NICUs in the network	29	30	23	73	36	7	9	44
Number of inhabitants	Australia: 23 million NZ: 4.4 million	34 million	7.9 million	126 million	47 million	9.5 million	8 million	52 million
Number of births/year	Australia: 300,000 NZ: 60,000	380,863	166,000	1,071,304	497,023	110,000	80,000	687,000
Number of eligible NICU admissions/year (<32 wks gestation/<1500 g)	3,500	2,700	1,500	3,700	2,600	900	800	7,700

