### Ethics, data collection, and dissemination

All participating networks have obtained ethics/regulatory approval or the equivalent from their local granting agencies to allow for de-identified data to be sent to the iNeo Coordinating Centre at the Maternal-Infant Care Research Centre, Mount Sinai Hospital, Toronto, Canada. The Coordinating Centre has been granted Research Ethics Board approval for the development, compilation, and hosting of the iNeo dataset, and all networks have signed data transfer agreements with the iNeo Coordinating Centre. Privacy and confidentiality of patient and unit-related data will be of prime importance to the iNeo collaboration, and data collection, handling, and transfer will be performed in accordance with the Canadian Privacy Commissioner’s guidelines, the Personal Information Protection and Electronic Documents Act, and any other local rules and regulations. No data identifiable at the patient level will be collected or transmitted, and only aggregate data will be reported. For all stages of the project, participating units will be assigned a code by their own network prior to data transfer into the iNeo dataset so that units remain anonymous within the iNeo collaborative. Following data analysis, findings will be disseminated within networks by their own network coordination team and not by the iNeo central team.

Following completion of the study in 2017, the data will be kept at the iNeo Coordinating Centre for a further two years before being returned to the originating networks unless otherwise agreed by the member networks.

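### The GEE clusters infants on the network, which is also the factor being compared, and the text does not say which model supplies the global and pair-wise network tests

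*Protocol article*

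**What the plan says.** The aim is to compare outcomes "among eight national neonatal networks spanning nine countries" (Network objectives). Under Comparisons between networks, three modelling sentences and one on multiplicity follow each other.

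- The tests of interest come first, and make the network the factor under study: "A global comparison, as well as pair-wise comparisons between networks, will be performed using multivariate regression models adjusted for confounders".
- The sentence after it fixes the level at which the GEE clusters, and that level is again the network: "Statistical models will employ generalized estimating equations to adjust analyses for clustering of infants within networks".
- A second kind of model is then added, and it is the only one of the two that reaches down to the NICU: "In addition, hierarchical random-effects regression models will be used to allow for variation at the network and unit level".
- The last sentence of the four deals with multiplicity and refers to neither kind of model by name; it prescribes a Bonferroni correction for the pairs of networks.

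No variance estimator is named for the GEE, and no sentence ties the global test or the Bonferroni-corrected pair-wise tests to one of the two kinds of model. Participating networks gives "a total of 251 NICUs in nine countries". On unit identity, the section Ethics, data collection, and dissemination states: "participating units will be assigned a code by their own network prior to data transfer into the iNeo dataset". An anonymous unit identifier is therefore available for analysis.

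**The concern.** GEE with a robust variance learns about uncertainty from how independent clusters vary around the fitted mean. That needs many clusters, and several on each side of a comparison. Here there are eight clusters in all, and a pair-wise contrast sets one against one other. Once each network has its own term, nothing is left between clusters from which to estimate the variance of that term. The correlation that can be estimated, among infants treated in the same NICU, is not the level at which this GEE clusters.

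These models serve the comparison of the primary composite outcome and of the secondary outcomes. Standard errors that are much too small would report differences between national networks that are not there, and a Bonferroni correction cannot repair a standard error close to zero.

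**Working it through.** **Inputs.** Eight networks. Units from Table 1: 29 + 30 + 23 + 73 + 36 + 7 + 9 + 44 = 251. Yearly admissions from Table 1: 3,500 + 2,700 + 1,500 + 3,700 + 2,600 + 900 + 800 + 7,700 = 23,400; over four years 93,600, of which Canada has 10,800 and the others 82,800. Pairs: 8 × 7 / 2 = 28, so the Bonferroni level is 0.05/28 = 0.0018 if all pairs are tested. The article gives no unit-level intraclass correlation (ICC); 0 to 0.05 is assumed.

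**The plan's own figure.** The power section gives detectable differences of 0.004 to 0.02 (Canada against all others) and 0.007 to 0.03 (Canada against one other network). Two proportions, independent infants, two-sided 5% and 80% power give 0.0031 (rate 1%) and 0.0141 (rate 40%) against 82,800, and 0.0062 and 0.0277 against 3,200. These agree with the stated values after rounding up to one significant figure. The figures therefore treat infants as independent and carry no allowance for clustering.

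**Why the robust variance fails.** The robust variance is H⁻¹ (Σ S_g S_gᵀ) H⁻¹, where S_g is cluster g's contribution to the estimating equations. Give each network its own indicator. The equation for that indicator draws on that network's infants only, that is, on one cluster, and fitting sets it to zero. So every S_g is zero in the network positions.

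- Without covariates the whole middle matrix is zero, and so is the standard error of every contrast. Computed values were about 1e-14 or smaller, under both independence and exchangeable working correlation.
- With covariates, a contrast inherits only the uncertainty of the covariate coefficients, passed on through differences in case mix. This is small, and grows as case mix differs more.
- The global test has 8 − 1 = 7 degrees of freedom. With fewer than seven covariate terms its robust covariance matrix is singular.

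**Simulation.** All set-ups use the Table 1 networks, units and admissions, and no true network effect. Entries are per-comparison type I error at a nominal 5%.

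| Set-up | Network clusters | Infants independent | NICU clusters |
|---|---|---|---|
| A: one covariate with case-mix shift; ICC 0, 0.01, 0.02, 0.05; 40 runs each | 91.8, 95.7, 97.5, 98.2% | 4.3, 27.9, 34.6, 56.8% | 6.4, 5.4, 5.7, 4.3% |
| B: one covariate; base rate 35%; ICC 0.005 to 0.02; 200 runs each | 99.7 to 99.9% | 24 to 47% | 6 to 7% |
| C: one covariate; ICC 0.005 to 0.02; 60 runs each | 98 to 99% | 20 to 44% | 7 to 9% |
| D: five covariates; ICC 0.01; case-mix shift SD 0, 0.2, 0.4; 10 runs each | 100, 92, 81% | not run | not run |

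In set-up A the unit variance on the log-odds scale is ICC/(1 − ICC) × π²/3. At ICC 0.01 the contrasts had an empirical SD of 0.0614. The mean standard errors were 0.0021 (network clusters), 0.0345 (infants independent) and 0.0611 (NICU clusters). As a check by hand, 1.96 × 0.0345/0.0614 = 1.10, which a standard normal exceeds in absolute value 27% of the time; 1.96 × 0.0021/0.0614 = 0.067, exceeded 95% of the time. Both agree with the table.

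In set-up B, family-wise error after Bonferroni was 100% (network clusters), 56 to 96% (infants independent) and 8% (NICU clusters).

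**The case against.** The strongest reply is that the article never commits to the combination that fails. It names neither fixed network indicators nor a robust variance, and a condensed article may leave both to an analysis plan. It also adds hierarchical models with unit-level variation, and the Bonferroni sentence comes after that addition. The network tests might come from those models.

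Much of this stands, and it limits what can be inferred:

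- A reader might infer that the plan ignores clustering within NICUs. It does not: that is true of the GEE sentence only. The hierarchical models allow for unit variation, and the later association analyses also plan random-effects models for unit-specific factors.
- A reader might infer near-certain false positives. That needs fixed network terms, a robust variance and inference from the GEE. Even then the rate depends on the covariates, falling to 81% in the set-up with the largest case-mix differences. The section on baseline adjustment itself expects case mix to vary.
- A reader might infer that these tests pick the best-performing networks. No section says so. Networks above or below average are flagged by standardized ratios and funnel plots, and practice changes are selected through a collaborative process.
- A reader might extend the point to the funnel limits. The article gives no formula for them, so nothing shows that they assume independent infants.

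What does not stand is that the ambiguity makes the GEE sentence harmless. The cluster level is stated, not left open. Pair-wise contrasts require a term per network, and a robust variance is the usual choice with GEE. A model-based variance avoids the collapse but understates uncertainty if units differ, and the plan's second aim looks for outcome-related differences between sites. Listing a second model does not make the first valid, and no order of precedence is given if they disagree.

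**Conclusion.** The point holds in this limited form: the GEE is clustered at the level being compared, and the model behind the global and pair-wise tests is not designated. Under fixed network effects and a robust variance, the collapse is algebraic and does not depend on any assumed ICC. Type I error was still 91.8% at ICC 0, and roughly 80% to near 100% across all set-ups. Under a model-based variance the error does depend on the ICC: close to nominal at 0, and about 20% to 57% for 0.005 to 0.05. These ICCs, the base rates, the covariate effects and the case-mix shifts are assumptions, and set-up D rests on only 10 runs per setting. The direction and the severity are secure; the exact percentages are not.

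**What to change.** State which model supplies the global and the Bonferroni-corrected pair-wise tests, and correct its cluster level. Either of these will do:

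1. GEE with network as a fixed effect and the NICU (251 coded units) as the cluster, with a small-sample variance correction because Sweden and Switzerland have only 7 and 9 units. NICU clustering gave 4% to 9% type I error in the simulations; the upper end supports the correction.
2. The hierarchical model, with NICU random intercepts and fixed network effects, named as the basis for the network contrasts.

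The change takes a sentence or two and one model option, with no new data, since units are already coded. The price is precision. In set-up A at ICC 0.01 the standard error rises from 0.0345 (infants independent) to 0.0611, a factor of 1.8.

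For planning, the design effect 1 + (m − 1) × ICC (ICC here on the proportion scale) with Canada's m = 10,800/30 = 360 and ICC 0.01 is 1 + 359 × 0.01 = 4.6. Applying each network's own design effect, the detectable differences become about 0.0074 to 0.030 for Canada against all others, and 0.015 to 0.059 against the smallest network. That is still informative, but the stated power figures should be read with this in mind.

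### The Bonferroni correction for pair-wise network comparisons is valid but slightly less powerful than necessary; Holm gives the same error control and never rejects fewer pairs

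*Protocol article*

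**What the plan says.** The objectives (Network objectives) are to compare outcomes "among eight national neonatal networks spanning nine countries". The analysis section (Comparisons between networks) plans both an overall test and all pairs: "A global comparison, as well as pair-wise comparisons between networks, will be performed using multivariate regression models adjusted for confounders". Multiplicity is then settled in one sentence: "Statistical significance will be evaluated by applying a Bonferroni correction to account for multiple pair-wise comparisons". The article mentions no step-down version. It does not say whether the family is the set of pairs within one outcome or extends across outcomes.

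The same section has a second route to unusual networks. Each network's observed rate is set against the rate expected from all other networks by indirect standardisation, and the ratios are shown on funnel plots with 95% and 99% prediction intervals.

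The power section (Statistical power for outcome comparisons) gives detectable differences "with statistical power of 80% assuming 5% type I error rate" and does not mention the correction.

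**The concern.** Single-step Bonferroni holds every pair to the same strict threshold, however many other pairs have already been shown to differ. Holm relaxes the threshold after each rejection and still keeps the family-wise error at 5%, with no added assumption about how the tests depend on each other. Where two procedures give the same protection and one always rejects at least as many hypotheses, fixing the other gives up some power.

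At stake are a few pair-wise differences that would be declared under Holm but not under Bonferroni. Power is tightest for pairs that involve the smallest networks, which have about 3,200 admissions over four years.

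**Working it through.** **Inputs from the article.** There are eight networks. Table 1 gives yearly eligible admissions of 3,500; 2,700; 1,500; 3,700; 2,600; 900; 800; 7,700, which sum to 23,400. Over four years that is 4 × 23,400 = 93,600, of which Canada has 10,800 and the others 82,800, as the power section states. Tests are two-sided at 5%, with outcome rates from 1% to 40%.

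**Inputs assumed.** The family is the pairs within one outcome. The spread of true rates between networks is not in the article, so it was varied.

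**The article's own figures first.** Solving the two-proportion normal approximation (pooled variance under the null) for 80% power at unadjusted 5%, with base rates of 1% and 40%:
- Canada against all others: 0.0031 and 0.0141 (stated: 0.004 to 0.02).
- Canada against 3,200: 0.0062 and 0.0277 (stated: 0.007 to 0.03).

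Both stated ranges are reproduced if rounded up to one significant digit. At 0.05/28 the Canada against 3,200 comparison needs 0.0091 and 0.0393. The stated differences of 0.007 and 0.03 then have power of about 0.54 and 0.47, against 0.87 and 0.86 at 5%. Power for the smallest pairs is therefore limited under the correction.

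**Thresholds.**
- Number of pairs: 8 × 7 / 2 = 28.
- Bonferroni: 0.05/28 = 0.001786 for every pair, critical z = 3.124.
- Holm: order the p-values and compare them in turn with 0.05/28, 0.05/27, ..., 0.05/1, stopping at the first failure. The first step is identical to Bonferroni (z = 3.124), the second is z = 3.113, and the last is 1.960. Any pair with p ≤ 0.05/28 passes under Holm too, so Holm's rejections always include Bonferroni's.
- Single-step joint (Tukey-type) value for eight groups: studentized range (8 groups, infinite degrees of freedom, 95%) divided by √2 = 3.031. Against 3.124, intervals are about 3% narrower (3.031/3.124 = 0.970).

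**Size of the gain.** There were 4,000 simulated data sets per scenario, with four-year admissions from Table 1 and unadjusted two-proportion tests. Mean number of true differences found:

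| Base rate | Assumed spread of true rates | True pairs | Bonferroni | Holm | Gain in pairs | Relative gain |
|---|---|---|---|---|---|---|
| 1% | ±5% | 28 | 0.10 | 0.10 | 0.00 | 0% |
| 1% | ±30% | 28 | 4.69 | 4.94 | 0.25 | 5.3% |
| 10% | ±10% | 28 | 5.82 | 6.11 | 0.29 | 5.0% |
| 10% | ±20% | 28 | 14.65 | 15.65 | 1.00 | 6.8% |
| 40% | ±10% | 28 | 17.37 | 18.72 | 1.35 | 7.8% |
| 40% | ±20% | 28 | 24.18 | 26.18 | 2.00 | 8.3% |
| 5% | one network 20% higher | 7 | 3.54 | 3.62 | 0.08 | 2.3% |
| 40% | one network 20% higher | 7 | 7.00 | 7.00 | 0.00 | 0% |

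With no true differences, the family-wise error was the same for both methods, 0.03 to 0.04. Shaffer's procedure, which also uses the logical links between pairs (divisors 28, then 21 seven times, then 16 five times, and so on), added little beyond Holm: 6.23 against 6.11 at 10% and ±10%, and 26.18 for both at 40% and ±20%.

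**The case against.** The strongest reply is that nothing here is wrong. Bonferroni is a standard, pre-specified control of the family-wise error, and it brings simple simultaneous intervals that always agree with the tests. Step-down tests do not offer that. This stands, and it limits the point to efficiency.

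The gain is also small in absolute terms. All methods of the Holm type start at 0.05/28, so the first difference is no easier to find, and help comes only once other pairs have been rejected. This stands as well.

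A reader might infer that real network differences are being missed for nothing. The documents do not support that: the loss is at most about two pairs in the scenarios examined, it vanishes where power is near 100%, and the matching intervals are a real return. A reader might also infer that the pair-wise tests are how the study decides which networks differ. They are one route. The article also identifies networks above or below average by indirect standardisation and funnel plots, and it leaves the choice of practice targets to a collaborative process.

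The simulations leave out covariate adjustment and clustering, whereas the article plans adjusted GEE and hierarchical models. That affects the size of the gain but not the guarantee that Holm never rejects fewer pairs for the same set of p-values.

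Finally, the gap between the power section's unadjusted 5% and the corrected tests is a separate matter. Holm would not close it, because its first step is the same 0.05/28.

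**Conclusion.** The point holds as a modest improvement. The Bonferroni correction is valid but slightly less powerful than necessary, because Holm gives the same family-wise control under the same conditions and rejects every pair that Bonferroni rejects. Under the assumed spreads the gain is about 0 to 2 of 28 pairs, or roughly 0% to 8%, with none for the first rejection and none where power is already near 100%. The size rests on three assumptions: a family of 28 pairs per outcome, which is inferred; the assumed spread of true rates; and independent, unadjusted data. The ordering of the two methods rests on none of them.

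**What to change.** Name one procedure and its family. For example, replace the sentence with: *Within each outcome the pair-wise comparisons will be tested by the Holm step-down procedure at family-wise 5%.*

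If tests and simultaneous intervals must agree, use instead one single-step joint-distribution (Tukey-type or max-T) critical value for both, about 3.03 against 3.12. The two should not be mixed. Holm's first step needs z = 3.124 and its last 1.960, while the joint value stays at 3.031. A pair could therefore be non-significant with an interval that excludes no difference, or significant with an interval that includes it.

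The cost is one sentence and standard software, with no loss of family-wise control. The downsides are small: Holm has no simple matching simultaneous intervals, and the joint method relies on the estimated joint distribution of the contrasts from the fitted model.
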